### Statistical analysis

Summary statistics will be calculated and reported in accordance with the Consolidated Standards of Reporting Trial (CONSORT). The baseline comparability between groups will be tested among descriptive characteristics, as well as baseline outcome measures. The intention to treat analysis will be performed by a blinded statistician. Missing values will not be imputed unless the amount of that for an outcome is over 5%, for which multiple imputation will be performed. Quantitative data will be expressed as the Mean (SD), and number plus percentage will be used to describe nominal data. The treatment effect will be evaluated by the change in primary outcome between group analyses, using independent t-test and ANCOVA for quantitative variables and the χ^2^ test or the Fisher exact test to adjust for demographic data such as age, sex, education background, literacy level, joint symptoms, comorbidities, type and duration of treatment on change in outcomes. Repeated measure effect will be evaluated by the repeated measures ANOVA or generalized estimating equation, where applicable. Correlations between data on usability of the educational tool and patient reported outcomes will be analyzed using linear regression analysis within the intervention group. Constructivist grounded theory and a relational ethics lens will guide the plan for qualitative analysis [31]. The QSR NVivo 12 software will be used to organize and store the qualitative data. Memo-writing will be used to develop and refine key conceptual categories, outline themes under which each category lies and analyze relationships across these key conceptual categories. This conceptual framework will draw attention to understanding user experiences and engagement with the intervention in a context of relational settings. A statistical analysis plan will be posted on a public data repository before analysis.

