### Outcome assessment

Outcome measures will be assessed at five time points through an online link powered by Wenjuanxing (www.wjx.cn, a website like Surveymonkey), namely at baseline (T0), post-intervention/consultation (T1), 1 month (T2), 3- and 6-months (T3 and T4) follow-up after the randomization.

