#### Primary outcome

Primary outcomes included knowledge about disease and treatment options. The validated osteoarthritis (OA) patient knowledge questionnaire (PKQ-OA) [25] will be used, modified, and adapted to reflect the key learner content covered in the eHealth patient education tool. The questionnaire comprises 7 single choice and 14 multiple choice questions with 31 correct answers and details of the questionnaire could be found in Additional file 4. We modified the PKQ-OA closely according to the patient education information provided in the education center and the questions are relevant with the evidence-based information. Total knowledge scores will be obtained by summing the scores, range from 0 to 21. Five patients with knee osteoarthritis and three healthcare professionals will provide input on the prototype of eHealth tool regarding design, content and usability, from which data collected will be used to finalize the tool for the trial. Higher scores indicate greater disease knowledge, and scoring above 50% on the knowledge portion of the questionnaire will be classified as adequately informed [26].

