##### Sample size

Sample size calculation was conducted based on the between-group difference on primary outcome, assuming that participants in the intervention group will have a correct response rate of 55.3% compared to that of 39.5% in the control group [27]. Based on a power of 95% and a 5% significance level (two-sided test), a value of 0.5 SD was used to ensure a large enough sample size. A Z-score of 1.96 was determined by applying these parameters. To allow for a dropout rate of 20%, a sample size of 108 per group (total of 216 participants) is required. Calculations were performed with PASS 15.0 (NCSS, LLC).

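### The between-group analysis of change in knowledge does not name the baseline PKQ-OA score as a covariate, giving up precision that the T0 measurement could supply at no cost

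*Protocol article*

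**What the plan says.** All points below are from the protocol article.

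- **Response and tests** (Statistical analysis): "The treatment effect will be evaluated by the change in primary outcome between group analyses, using independent t-test and ANCOVA for quantitative variables".
- **Covariates** (same sentence): "to adjust for demographic data such as age, sex, education background, literacy level, joint symptoms, comorbidities, type and duration of treatment on change in outcomes". Grammatically this clause follows the χ² and Fisher tests, which cannot adjust for covariates, so I read it as describing the ANCOVA. The list is given as examples. It names eight items, and baseline knowledge is not one of them.
- **Availability of baseline** (Outcome assessment): measurements are taken "namely at baseline (T0), post-intervention/consultation (T1), 1 month (T2), 3- and 6-months (T3 and T4) follow-up after the randomization".
- **Outcome scale** (Primary outcome): "Total knowledge scores will be obtained by summing the scores, range from 0 to 21".
- **Other stated use of the baseline score** (Statistical analysis): "The baseline comparability between groups will be tested among descriptive characteristics, as well as baseline outcome measures".

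The Statistical analysis section also announces that a separate analysis plan will be posted before analysis. That plan is not at hand.

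**The concern.** The baseline knowledge score is measured in everyone and is likely to be among the best predictors of later knowledge. As written, it enters the treatment comparison only by subtraction, and a between-group test of baseline values does nothing to correct an imbalance. Subtraction imposes a coefficient of 1 on baseline, whereas the coefficient that minimises variance is r when the two variances are equal. For any r below 1 the change score therefore over-corrects. Two things follow: the estimate is noisier than it need be, and it moves in the opposite direction to any chance difference between arms at T0. What is at stake is the width of the confidence interval for the main result and possibly the power.

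**Working it through.** **The plan's own figure.** The Sample size section assumes a "correct response rate of 55.3% compared to that of 39.5% in the control group", and continues "Based on a power of 95% and a 5% significance level (two-sided test" and "a value of 0.5 SD was used to ensure a large enough sample size". It arrives at 108 per group with 20% dropout. Reading 0.5 SD as a standardised difference, n = 2(1.96+1.645)²/0.5² = 104 per arm (105 by the t distribution), or 104/0.8 = 130 (132) after dropout. So 108 is not reproduced at 95% power. It is matched by 90% power with a two-sided t-test: 86/0.8 = 107.5, rounded up to 108. That discrepancy is a separate matter. I need only the number of completers, 108 × 0.8 ≈ 86 per arm.

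**Variances.** Let s be the SD of the score, equal in both arms and at both times, and r the within-arm correlation of baseline with follow-up.

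- Follow-up score alone: s²
- Change: 2(1−r)s²
- ANCOVA with baseline score: (1−r²)s²
- Ratio of ANCOVA to change: (1−r²)/[2(1−r)] = (1+r)/2

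The ratio is below 1 for every r below 1. Change is noisier than the follow-up score alone when 2(1−r) > 1, that is, when r < 0.5.

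**Power if 0.5 SD is an SD of the score.** Power = Φ(0.5·√(86/2)/√v − 1.96), with v the variance factor above and 0.5·√43 = 3.279. For r=0.3, change: 3.279/√1.4 − 1.96 = 0.81, giving 79.1%. ANCOVA: 3.279/√0.91 − 1.96 = 1.48, giving 93.0%.

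| r (assumed) | Variance ratio | Power, change | Power, follow-up only | Power, ANCOVA | Completers per arm for 95% power, change vs ANCOVA |
|---|---|---|---|---|---|
| 0.3 | 0.65 | 79.1% | 90.6% | 93.0% | 146 vs 95 |
| 0.5 | 0.75 | 90.6% | 90.6% | 96.6% | 104 vs 78 |
| 0.7 | 0.85 | 98.8% | 90.6% | 99.6% | 63 vs 54 |
| 0.9 | 0.95 | >99.9% | 90.6% | >99.9% | 21 vs 20 |

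These are normal approximations; at r=0.5 the t distribution gives 90.3% for change.

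**Power if 0.5 SD is an SD of change.** The t-test on change then has 90.6% power whatever r is. Adding the baseline score raises this to 98.2% (r=0.3), 96.6% (r=0.5) or 94.5% (r=0.7). There is still a gain, but change does not fall below about 90%.

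**Chance imbalance.** Given an observed baseline difference D between arms, the expected change-score estimate is the true effect minus (1−r)D; the ANCOVA estimate has no such shift. With 86 per arm, one standard error of D is √(2/86) = 0.152 SD. An imbalance of that size shifts the change estimate by 0.7 × 0.152 = 0.107 SD at r=0.3, 0.076 SD at r=0.5 and 0.046 SD at r=0.7. Against an effect of 0.5 SD these are about 21%, 15% and 9%. Averaged over randomisations, the shift is zero.

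**The case against.** The strongest reply has four parts.

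1. **The list is open and the analysis plan is unseen.** The covariates are examples under a demographic label, where one would not look for a baseline outcome score. An ANCOVA of change may also include baseline. So the article does not exclude baseline adjustment, and the analysis plan may add it. That is true, but the response, the tests and eight covariates are positively stated, and followed as written they give a weaker analysis than the data allow. A better method that costs nothing is worth stating here.
2. **Baseline is not thrown away.** A reader might infer that the T0 measurement is discarded. It is not: change uses it with slope 1. At r=0.7 change is clearly better than follow-up alone (98.8% vs 90.6%), and at r=0.9 only 5% of variance is lost.
3. **The comparison above is with unadjusted change.** The planned ANCOVA includes education and literacy, which may be correlated with baseline knowledge and so recover some of the loss. The documents give nothing from which to quantify this.
4. **The power loss rests on assumptions.** A reader might infer that the trial is underpowered by this choice, or that a low r is to be expected because one arm is taught. The article gives no r, and a uniform shift in one arm does not by itself lower the within-arm correlation. Nor does it say which SD the 0.5 refers to.

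A reader might also take the t-test to be the primary analysis. The sentence names the t-test and the ANCOVA side by side and ranks neither.

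**Conclusion.** The point holds as a free gain in efficiency. The stated analysis of change, without the baseline PKQ-OA score among its named covariates, is less precise than a baseline-adjusted ANCOVA for any r below 1. Relative to unadjusted change, the variance that would remain is 65% at r=0.3, 75% at r=0.5, 85% at r=0.7 and 95% at r=0.9. This assumes equal variances, large samples and an r that the document does not supply; the planned covariates may narrow the gap. The analysis is also needlessly sensitive to chance imbalance at T0. It is not biased on average, and the validity of the trial is not in question. A power shortfall cannot be asserted: it requires both an r below about 0.5 and reading the 0.5 SD as an SD of the score.

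**What to change.** State in the Statistical analysis section, or in the analysis plan before it is posted, that PKQ-OA at the follow-up time point designated as primary, and likewise at the other time points, will be compared between arms by ANCOVA of the follow-up score. The model contains randomised arm, the baseline PKQ-OA score as a mandatory covariate, and those of the named covariates that are fixed before randomisation. Report the adjusted difference with its 95% CI. Keep the t-test on change as descriptive support only.

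If the sponsor prefers change as the response, the same model with baseline as a covariate gives the identical treatment estimate, so the reported quantity need not alter. The sentence must say which of T1 to T4 is the primary time point. T0 is already collected, so there are no new data, visits or patients. The cost is the wording and one degree of freedom.

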### Participants and setting

We will recruit 216 participants referred to the outpatient physiatry/physiotherapy clinic at West China Hospital, Sichuan University in Southwest China. Ethics approval was obtained from Ethics Committee on Biomedical Research, West China Hospital of Sichuan University, and prospectively registered on the Chinese Clinical Trials Registry (ChiCTR2100051083) registered 12.09.2021. Potential participants will be identified from clinic schedules and asked on site to assess their eligibility and to obtain written consent.

To be included, potential participants must present with one of the following: (1) be aged over 45 years, (2) have knee osteoarthritis (Kellgren-Lawrence grade 2 or greater) with symptoms lasting for at least 3 months, (3) is able to provide informed consent, (4) be fluent in verbal and written Chinese, (5) with adequate hearing and eyesight, (6) own an internet-capable device and with access to internet, (7) is not included in the waitlist of knee replacement surgery, (8) be in an independent ambulatory status.

Potential participants will be excluded if they have any of the following: (1) not able to read or speak Chinese, (2) had a history of clinic visits or an appointment with any physician/therapist/healthcare professional for evaluation of knee osteoarthritis, (3) had a diagnosis of fibromyalgia or a systematic arthritic condition, (4) had a history of surgery related to knee, hip and other joints.

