### Usual care group

The control group will receive usual care including the wide range of care practices provided in the outpatient clinic at West China Hospital which are unrestricted by study protocols, which is in contrast to standard care may not reflect real-world care [23]. Participants in this group will be required to record treatment received using a log sheet weekly over the course of the study period. The common practice consists of a visit to a physiatrist or physiotherapist at outpatient clinic, verbal information about knee osteoarthritis and treatment options, prescription of pain medication, may involve physical or occupational therapy (e.g., manual therapy, physical agents) and advice about home exercises. All participants in the control group will be contacted via telephone or WeChat messenger (Tencent Holdings Ltd., Shenzhen, China) by an assistant who will provide instructions for the participant on how to finish the follow-up questionnaires and access the planned care they were seeking for knee osteoarthritis.

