#### Other measures

Participants’ demographic data, history of diseases and health behavior information will also be collected. Potential “inadequate health literacy level” in participants will be screened using 3 questions: “how confident are you filling out questionnaires by yourself?” (“Confident with Questionnaires”), “Do you need someone to help you read? If yes, how often?” (“Read Assistance”) and “Do you have obstacles learning about your medical condition due to your inability to read? If yes, how often?” (“Problem Reading”) [28, 29]. In the process evaluation, measures of recruitment rate, attendance and follow-up rate will be monitored and recorded. Reasons for exclusions, declining participation and the drop-out of participants will be noted through the trial.

Participants in the eHealth intervention group will receive additional questions on the usability of the tool, including 13 closed questions and 3 opened-ended questions [30] and details of the questionnaire could be found in Additional file 4. Web-based analytics generated by the educational tool will be used to assess the utilization of the tool, which include data on content with which they engage, length of time spent on different content, and satisfaction ratings or feedback.

The measure of opinion and perspectives for participating the trial will be assessed via a phone- recorded interview (semi-structured) in both the eHealth and usual care group with the interviewee’s permission, for which a guide with open questions will be used to provide structure. The phone call will be made by a researcher who have experiences in qualitative interviews and is independent of the conduction of this trial. Two researchers (independent of the conduction of this trial) will be instructed by the interviewer to independently read and code transcribed texts line-by-line, from which codes generated will be sorted into themes and discussed to gain an overall understanding of any issue on difficulties and barriers to complete the trial. Any discrepancy will be resolved by the interviewer (senior researcher). During the trial, adverse events, medications and any other care received will be recorded using a log sheet, a sample could be found in Additional file 3.

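### The treatment effect is to be adjusted for type and duration of treatment, most naturally a post-randomisation variable, and covariate adjustment is assigned to tests that cannot adjust

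*Protocol article*

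**What the plan says.** All references are to the protocol article.

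- **Statistical analysis, population.** "The intention to treat analysis will be performed by a blinded statistician".
- **Statistical analysis, methods.** The effect is judged on the between-group change in the primary outcome, "using independent t-test and ANCOVA for quantitative variables". The same sentence goes on to the chi-square test or "the Fisher exact test to adjust for demographic data such as age, sex", and the list continues "education background, literacy level, joint symptoms, comorbidities, type and duration of treatment on change in outcomes". It does not say when type and duration of treatment are measured, does not confine covariates to baseline values, and does not say whether the t-test or the ANCOVA is primary.
- **Participants and setting.** A person is excluded who "had a history of clinic visits or an appointment with any physician/therapist/healthcare professional for evaluation of knee osteoarthritis".
- **Usual care group.** "Participants in this group will be required to record treatment received using a log sheet weekly over the course of the study period". Usual care is not constrained by the protocol.
- **eHealth intervention group.** The tool has a self-management feature in which planned care received for the knee is logged.
- **Other measures.** "During the trial, adverse events, medications and any other care received will be recorded using a log sheet".

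**The concern.** An intention-to-treat comparison estimates the effect of being assigned to the tool, through whatever routes that effect takes. A covariate fixed before randomisation leaves that target intact. A covariate that allocation can alter does not. Conditioning on it removes the part of the effect that passes through it. If an unmeasured factor such as motivation drives both care uptake and knowledge, conditioning also creates an association between arm and that factor, which randomisation had removed.

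Here allocation could plausibly alter treatment. The Abstract presents patient education as an aid to treatment decisions and lists compliance with treatment among the things the tool is to be evaluated on. Because the protocol does not rank the t-test and the ANCOVA, the affected estimate could become the headline result.

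A second, independent fault is that the sentence attaches covariate adjustment to chi-square and Fisher exact tests. The Primary outcome section defines a binary classification (adequately informed, above 50% on the knowledge score). An adjusted comparison of it cannot be run with the tests named.

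**Working it through.** **Step 1: when is treatment measured?** The protocol does not say, so the sections have to be read together.

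- Before entry: the exclusion criterion removes people with earlier visits or appointments for evaluation of knee osteoarthritis. Professional treatment for the knee should therefore mostly start at or after entry.
- Data collected on the participant, in Other measures: demographics, history of diseases and health behaviour. Prior treatment is not named.
- During the study: three treatment records are described, namely the weekly sheet in the control arm, the log inside the tool, and the trial log sheet.

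Every treatment record described is a follow-up record. Post-randomisation treatment is the natural reading, though it remains an inference.

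**Step 2: what would adjustment do?** The plan gives no figure on this point, so there is none to reproduce. The following is an illustration. From the plan come the 0.5 SD effect (Sample size) and about 86 completers per arm (108 × 0.8 = 86.4). Three quantities are not in the documents and are assumed:

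- *a*: effect of allocation on the treatment covariate, 0 to 0.5 SD
- *b*: effect of that covariate on knowledge, 0 to 0.3
- *u*: loading of an unmeasured shared cause on both, 0 or 0.4

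In a linear model with unit within-arm variances and a total effect of 0.50, the coefficient for arm after adjustment is

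adjusted effect = 0.50 − *a·b* − *a·u*²

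The second term is the effect routed through treatment; the third is the path opened by conditioning.

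| *a* | *b* | *u* | Formula | Simulated, adjusted | Simulated, unadjusted |
|---|---|---|---|---|---|
| 0 | 0.3 | 0 | 0.50 | 0.50 | 0.50 |
| 0 | 0.3 | 0.4 | 0.50 | 0.50 | 0.50 |
| 0.3 | 0.3 | 0 | 0.50 − 0.09 = 0.41 | 0.41 | 0.50 |
| 0.5 | 0.3 | 0 | 0.50 − 0.15 = 0.35 | 0.34 | 0.49 |
| 0.5 | 0 | 0.4 | 0.50 − 0.08 = 0.42 | 0.42 | 0.50 |
| 0.5 | 0.3 | 0.4 | 0.50 − 0.15 − 0.08 = 0.27 | 0.26 | 0.49 |

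(2,000 replicates per row.) Leaving the covariate out recovers the effect in every row. Including it does harm only when *a* is not zero. The direction is not fixed either: with *a* = 0.3, *b* = −0.3 and *u* = 0 the formula gives 0.50 + 0.09 = 0.59.

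**Step 3: can the named tests adjust?** A chi-square or Fisher exact test of arm against a binary outcome uses the cell counts of one table. Covariates do not enter it. Of the methods in that sentence, only ANCOVA adjusts. The next sentence names generalized estimating equations for repeated measures; these can model a binary outcome with covariates, but the protocol does not assign them that task.

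**The case against.** - **The timing is inferred.** Treatment appears in a list introduced as demographic data. The exclusion covers professional evaluation, not self-treatment, and symptoms must have lasted at least 3 months, so some earlier self-treatment is possible. This stands, and makes a baseline reading possible though less likely. If that was meant, the text has to say so.
- **Bias is not demonstrated.** A reader might infer that the adjusted estimate is biased. The documents do not support that. Bias requires allocation to change treatment type or duration, and treatment to affect knowledge or share a cause with it; neither size is given. What can be said is that the estimate may be biased and no longer targets the total effect.
- **The test error biases nothing.** A reader might take the chi-square and Fisher wording as a further cause of bias. Those tests simply give an unadjusted comparison, which randomisation protects. Nor is it right that no method for an adjusted binary analysis appears in the plan, since generalized estimating equations are named.
- **A power loss cannot be claimed.** One could suppose that 20-40% of the effect runs through later care, giving 0.40-0.30 SD and power of 74%-50% in place of 90% with 86 per group. The documents give no basis for that share, and those are powers of a plain two-sample test, not of an ANCOVA, whose residual variance differs. The outcome is a questionnaire fitted to the tool's content, and the first follow-up questionnaire goes out one day after a consultation held within 7 days of randomisation, so little treatment can have accrued by then.
- **An unadjusted t-test sits alongside, and a statistical analysis plan is promised.** Both are true and limit the damage. Neither corrects a covariate the protocol itself names.

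**Conclusion.** The point holds in a limited form. The protocol names an adjustment variable that, on the most natural reading of its own eligibility and data-collection sections, is measured after randomisation and can be changed by allocation. An ANCOVA including it would not estimate the total intention-to-treat effect that the same section calls for. The possible bias ranges from none, if allocation does not affect treatment, to about half of a 0.50 SD effect in the most unfavourable scenario simulated. These values rest on assumed inputs and a linear model and are not a forecast for this trial. The t-test is untouched. Separately, the chi-square and Fisher exact tests are misdescribed as methods of adjustment, which needs correcting but distorts no estimate.

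**What to change.** In the Statistical analysis section, or in the promised statistical analysis plan before any analysis:

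1. Limit covariates to values measured before randomisation: baseline (T0) knowledge score, age, sex, education, literacy, baseline joint symptoms and comorbidities.
2. Remove type and duration of treatment from the model, unless it is expressly defined as treatment before randomisation. Report treatment received during the study by arm, descriptively.
3. State ANCOVA as the adjusted method for quantitative outcomes and logistic regression for binary outcomes, or generalized estimating equations where measures are repeated. Keep chi-square and Fisher exact tests as unadjusted tests only.

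The cost is a sentence or two of rewording. No new data are needed: knowledge is already measured at T0 and treatment is already logged.

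### Repeated-measures ANOVA with no imputation at 5% missing or less can exclude about 5% to 18–20% of randomised participants from the longitudinal analysis, despite the stated intention-to-treat principle

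*Protocol article*

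**What the plan says.** Three statements in the protocol's Statistical analysis section bear on this point.

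- Analysis population: "The intention to treat analysis will be performed by a blinded statistician".
- Missing data: "Missing values will not be imputed unless the amount of that for an outcome is over 5%, for which multiple imputation will be performed".
- Longitudinal analysis: "Repeated measure effect will be evaluated by the repeated measures ANOVA or generalized estimating equation, where applicable".

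The between-group comparison is described in a separate sentence: "The treatment effect will be evaluated by the change in primary outcome between group analyses, using independent t-test and ANCOVA for quantitative variables".

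The Outcome assessment section fixes the schedule. "Outcome measures will be assessed at five time points through an online link powered by Wenjuanxing", "namely at baseline (T0), post-intervention/consultation (T1), 1 month (T2), 3- and 6-months (T3 and T4) follow-up after the randomization". That is one baseline and four post-baseline assessments.

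The Sample size section sets 108 per group, 216 in total, with an allowance of 20% for dropout.

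The protocol does not say whether the 5% is counted at each visit, over all visits together, or by participants with any gap. Nor does it say when ANOVA rather than GEE is to be used.

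**The concern.** Each rule looks ordinary alone. A low threshold for imputation does little harm in a single-visit comparison, and repeated-measures ANOVA does no harm when the data are complete. Together they allow a complete-case analysis. Small losses at each visit can stay at or below the trigger, so nothing is imputed, while the ANOVA discards every participant who missed any one of the visits.

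At stake is whether the longitudinal result describes the randomised groups. A participant with three of four follow-up scores contributes nothing, although those scores were collected. If missing a visit is related to arm and to knowledge, the remaining completers are no longer a randomised comparison.

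Scattered missed visits are plausible here. Follow-up is by self-completed online questionnaire, and the protocol already plans a reminder for non-response. Only the intervention arm receives the tool and twice-weekly prompts for at least 6 months. The Discussion accepts that some participants over 60 may find the technology difficult.

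**Working it through.** The protocol gives no figure for participants lost from the repeated-measures analysis, so there is none to reproduce.

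**Inputs.** From the protocol: N = 216 (Sample size), k = 4 post-baseline visits (Outcome assessment), and a threshold of more than 5% missing (Statistical analysis). Assumed: baseline scores are complete, and the ANOVA is the conventional kind that deletes any participant with a gap.

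**Largest count that does not trigger imputation.**
- Per visit: 0.05 × 216 = 10.8, so at most 10 participants (10/216 = 4.6%).
- Pooled over four visits: 0.05 × 4 × 216 = 43.2, so at most 43 missing scores of 864 (4.98%).

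**Share excluded by the ANOVA without imputation.**

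| How the 5% is counted | Pattern of misses | Calculation | Excluded |
|---|---|---|---|
| Per visit | Same people miss every visit | 10/216 | 4.6% |
| Per visit | Independent, 10 per visit | 1 − (1 − 10/216)^4 | 17.3% (about 37) |
| Per visit | Independent, exactly 5% per visit | 1 − 0.95^4 | 18.5% (about 40) |
| Per visit | Never overlapping, 10 per visit | 4 × 10/216 = 40/216 | 18.5% |
| Pooled | Each miss in a different person | 43/216 | 19.9% |
| Participants with any gap | Any | 10/216 | 4.6% |

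Ignoring whole-number limits, the non-overlapping case gives 4 × 5% = 20%, and the same-people case and the any-gap reading give 5%. The range is therefore about 5% to about 18–20%.

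**Same data under GEE.** With 5% missing independently at each visit, a participant lacks all four scores with probability 0.05^4 = 0.00000625. GEE therefore keeps essentially every participant and 95% of the observations.

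**Same data in a single-visit comparison.** A t-test or ANCOVA on change at one visit loses only those missing at that visit: at most 10/216, about 5%, when the rule is applied per visit.

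**The case against.** The case against has several parts.

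*GEE is already listed.* This is correct. A reader might infer that both named methods drop participants, but GEE uses every observed visit. Its limit is different: without weighting it assumes data missing completely at random. The protocol does not commit to GEE, however, so the complete-case route stays open.

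*It is not the treatment-effect analysis.* This stands. The protocol evaluates the treatment effect by t-test and ANCOVA on change. A reader might carry the 18–20% loss over to that comparison and infer a matching loss of power. The documents do not support this, because a single-visit test does not delete people for gaps at other visits.

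*The planned 20% dropout would trigger imputation.* This mostly stands. Counted per visit, 20% missing at T4 is well over 5%, so multiple imputation applies there. Counted pooled, the trigger is also passed unless essentially all the loss falls at T4 alone. A reader might infer that the trial's expected dropout leads to a completers-only estimate at T4, but on a per-visit count the plan would not produce one. The gap lies at low missingness. On a per-visit count, early visits could also stay unimputed while later ones are imputed.

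*The size of any bias.* A reader might want a bias in SD units. The documents give neither the correlation between visits nor a missingness mechanism, and the answer changes with whether raw scores, change or baseline-adjusted scores are compared. No bias figure is therefore claimed.

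*The detail belongs in the later analysis plan.* The protocol does promise one, and how the 5% is counted could properly be settled there. But naming repeated-measures ANOVA and barring imputation at or below 5% are positive choices. An analysis plan that follows them inherits the conflict.

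**Conclusion.** The point holds for the repeated-measures analysis only. The protocol permits repeated-measures ANOVA without imputation at or below 5% missing. Over four post-baseline visits this can exclude about 5% of the 216 randomised if the same people miss each visit, and about 18–20% if misses are scattered and the 5% is counted per visit or pooled. If the 5% counts participants with any gap, the loss is at most 5%. Any such exclusion of randomised participants with observed scores is contrary to the stated intention-to-treat analysis.

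The upper figures are near the ceiling: they need misses close to the threshold at every visit with little overlap. They also rest on conventional listwise deletion and complete baseline scores. The t-test and ANCOVA comparison is not affected to this extent. This should be changed because it is cheap to change, but it does not threaten the main between-group comparison.

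**What to change.** Delete the repeated-measures ANOVA option. For the knowledge score at T1–T4, specify a linear mixed model with arm, visit, arm-by-visit interaction and baseline score, fitted to all observed scores of all randomised participants. This analysis then no longer depends on the 5% trigger. Keep multiple imputation as a sensitivity analysis for it, whatever the amount missing.

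Choosing GEE alone would also stop the loss of participants. The mixed model is preferred because it needs data missing at random given the observed scores, whereas unweighted GEE needs them missing completely at random.

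Cost: a change of wording and standard software, with no new data or participants. The downside is slightly more modelling work and the missing-at-random assumption, which the data cannot confirm.
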